#### Participants randomization

This will be a randomized parallel group trial with a 1:1:1 allocation ratio. Randomization will be performed using a block randomization algorithm (block size of 15) based on Matlab random number generator (MATLAB version: R2014a, Natick, Massachusetts: The MathWorks Inc) to ensure quantitative symmetry of patients assigned to the three groups even during enrolment and to allow for balanced interim analyses. Randomization will be centralized and performed by an independent biostatistician not involved in the trial, from the Biomedical Engineering Unit. Each patient will be given a unique patient number and a randomization code for the allocation at enrolment, so that the staff enrolling participants will know which treatment each patient will be assigned to only once the patient has been enrolled [55]. Finally, the biostatistician responsible for generating the randomization list and the biostatistician responsible for analyzing the data will be unaware of the association between randomization codes and treatment group. Furthermore, to ensure examiner blinding to the study condition, group allocation will be also concealed using alphanumeric codes assigned by a project manager after randomization. Group anonymization will minimize bias in the administration of study measures.

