### Study setting

The study will be conducted at two specialized medical centers renowned for rehabilitation and a multidisciplinary approach: Istituti Clinici e Scientifici Maugeri IRCCS Pavia, Italy; Istituti Clinici e Scientifici Maugeri IRCCS Montescano, Italy.

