#### Intervention phase

The intervention phase itself will be conducted by the collaborative effort of the Neurophysiopathology, Psychology, and Neurorehabilitation Department at ICS Maugeri, spanning across Montescano (PV) and Pavia, Italy. Outcome measures will be administered at the Neurophysiopathology and Psychology Departments of ICS Maugeri in Montescano and Pavia (see Table 1).

After the assessment, patients willing to participate will be asked to sign a written informed consent in order to join the study. Consequently, participants will be randomly assigned to one of the three intervention groups (see the paragraph “Participants randomization” and Fig 1).

For motor rehabilitation, patients will be given precise instructions on the prescribed exercises by a physiotherapist during the first week at ICS Maugeri. In this initial week, the first session for each exercise will be supervised (pre-training). The pre-training is considered part of the intervention training. After this, patients will continue with the exercise routine independently on a weekly basis (see Table 2 for details).

**Table 2 pone.0306256.t002:** Weekly schedule per trial group.

		*Duration*	Day 1	Day 2	Day 3	Day 4	Day 5
			*Domain (s)*				
**Group 1** (90 min)	*Motor functions*	20 minutes	Fast-paced walking	Fast-paced walking	Fast-paced walking	Fast-paced walking	Fast-paced walking
		25 minutes	Balance and coordination	Postural control	Joint mobilization	Proprioception	Balance and coordination
		45 minutes	Muscle relaxation	Muscle relaxation	Muscle relaxation	Muscle relaxation	Muscle relaxation
**Group 2, Group 3** (90 min)	*Motor functions*	20 minutes	Fast-paced walking	Fast-paced walking	Fast-paced walking	Fast-paced walking	Fast-paced walking
		25 minutes	Balance and coordination	Postural control	Joint mobilization	Proprioception	Balance and coordination
	*Cognitive functions (paper-pencil or Khymeia VRSS Evo)*	45 minutes per day	Orientation Memory Attention/executive functions Visual-spatial functions	Memory Attention/executive functions Visual-spatial functions	Orientation Memory Attention/executive functions Visual-spatial functions	Memory Attention/executive functions Visual-spatial functions	Memory Attention/executive functions Visual-spatial functions

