### Data analysis

#### Sample size

The sample size was calculated considering the MMSE score, the primary outcome of the trial. We required the sample size to be large enough to detect a difference in efficacy (measured as MMSE at the end of treatment—MMSE at enrolment) of 1.4 MMSE points between the most effective treatment and the least effective treatment. This value was selected because it is reported in literature as the lowest threshold for the minimum clinically important difference (MCID) [39,53]. To be conservative, the third treatment was assumed to be as effective as the average of the other two. The aim was to detect this difference with a two-sided type I error of 5% and 80% power. From previous studies in populations similar to ours [54], the standard error of measurement (SEM) for the MMSE is 1 point, giving an SD of 1.41 (resulting in a Cohen’s effect size close to 1). The sample size was then estimated at 63 patients (21 per group). Taking into account the possibility of losing some patients (up to 16% of drop-outs), the required sample size was set at 75 patients (25 per group). Computations were performed using the ’proc power’ of the SAS statistical package with the following parameters: one-way ANOVA as statistical model, 0, 0.7 and 1.4 as group means, 1.41 as standard deviation, 0.05 as alpha and 0.8 as power (SAS/STAT, release 9.4, SA Institute Inc., Cary, NC, USA).

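### Allocation concealment is real but weakened at block ends: with one constant, published block size of 15, a full tally reveals the last place of every block

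*Protocol article*

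**What the plan says.** All the main statements are in the protocol article, section Participants randomization.

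- Design: "This will be a randomized parallel group trial with a 1:1:1 allocation ratio".
- Method: "Randomization will be performed using a block randomization algorithm (block size of 15", from a Matlab generator. The stated reasons are balance between groups during enrolment and at interim analyses. No variation in block size and no stratification by centre is mentioned.
- Who does it: "Randomization will be centralized and performed by an independent biostatistician not involved in the trial".
- What enrolling staff know: a patient number and randomization code are issued at enrolment, "so that the staff enrolling participants will know which treatment each patient will be assigned to only once the patient has been enrolled".
- Coding of groups: "to ensure examiner blinding to the study condition, group allocation will be also concealed using alphanumeric codes assigned by a project manager after randomization". The stated purpose is to blind examiners, not to conceal allocation from those who enrol.

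Elsewhere in the article: "The study will be conducted at two specialized medical centers" (Study setting); "the required sample size was set at 75 patients (25 per group" (Sample size); and, for motor training, "In this initial week, the first session for each exercise will be supervised (pre-training" (Intervention phase), with a similar supervised start for the cognitive exercises. The three arms are relaxation after motor training, paper exercises, and tablet exercises, so the arm is plain to whoever sees the treatment delivered.

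**The concern.** The assurance about enrolling staff concerns the next patient. It also implies that they come to know the arm of every patient already enrolled. Central generation hides the list but not this history. A constant block of 15 with five places per arm turns the history into information: once two arms have used their five places, the rest of the block is known.

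If someone who decides on enrolment can foresee the arm, a patient can be brought forward or held back, and the groups may then differ in ways that randomization was meant to prevent. The contrasts rest on 25 patients per arm. The Statistical analysis section relies on randomization for baseline comparability and adjusts only where a significant baseline difference is found. The Neurophysiopathology and Psychology Units select participants at baseline (Study timeline) and are also among the departments that run the intervention (Intervention phase), so knowledge of past allocations is plausible among selecting staff.

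**Working it through.** **Inputs.** Three arms, 1:1:1, block size 15 (Participants randomization); 75 patients, 25 per group (Sample size); two centres (Study setting).

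**The plan's own figure.** A one-way ANOVA with means 0, 0.7 and 1.4, SD 1.41 and alpha 0.05 has power 0.809 at 21 per group and 0.787 at 20, so 63 is reproduced. Then 63 / (1 − 0.16) = 75, which is 75 / 15 = 5 complete blocks. The article gives no figure for predictability.

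**Certain assignments, full tally and known block boundaries.** An assignment is certain when all remaining places in the block belong to one arm.

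- 15th place: 1
- 14th: 4/14 = 0.286 (2/7)
- 13th: (4×3)/(14×13) = 0.066
- 12th: (4×3×2)/(14×13×12) = 0.011
- 11th: (4×3×2×1)/(14×13×12×11) = 0.001

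The sum is 1.364 per block. Over five blocks: 5 × 1.364 = 6.8 of 75, or 9.1%.

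**At least one arm excluded.** With k places left, the probability is [3·C(10,k) − 3·C(5,k)] / C(15,k). This gives 1 for k = 1 and k = 2, 0.725 for k = 3, 0.451 for k = 4, 0.251 for k = 5, and falls quickly after that. The sum is 3.64 per block, or 18.2 of 75 (24%). This count includes the certain assignments.

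**Each centre sees only its own patients.** Assume one central unstratified list, an even random split between centres, and, generously, known block boundaries. A centre is certain only if all ten patients of the two exhausted arms, and the next patient, are its own. Expected number per block: 1.364 × 2 × 0.5^11 = 0.0013, so 0.007 of 75. With a 70/30 split, the larger centre has 5 × 1.364 × 0.7^11 = 0.13 of 75.

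**Block length.** With m places per arm in a block, the certain share under a full tally is 1/(2m + 1): 33.3% for block 3, 20.0% for 6, 14.3% for 9 and 9.1% for 15. The weakness is that the size is constant and known, not that it is 15.

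**Best guess.** Always guessing the arm used least so far is right about 50% of the time in simulation, against 33% by chance. This rule needs neither the block size nor the boundaries.

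**Effect of varied long blocks (12, 15, 18), by simulation with a full tally.** A recruiter who knows the three possible sizes but makes no use of the total is certain for about 1.1 of 75 and can exclude an arm for about 3.4. The guess rate is 49 to 50%. If the recruiter also uses the known total of 75, with sequences drawn at random from all those that sum to 75, the figures are about 2.5 and 7. If the sizes are fully unknown and only the total of 25 per arm is used, just the final block leaks: 3m/(2m + 1) = 1.33 to 1.38 assignments for m = 4 to 6.

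**The case against.** Central randomization by someone outside the trial, with a code issued at enrolment, is proper concealment, and 15 is a long block for three arms. Even with a full tally, about 91% of assignments cannot be deduced with certainty. The upper figure needs block boundaries and every allocation at both centres, and the article does not say that staff share or keep such records. A fixed block is a legitimate choice with a stated purpose. All of this stands, and it sets the point at minor. It does not remove the point: the article does not rule out shared knowledge, describes the intervention as joint work across the two sites, and does not say that lists are common to both centres. If lists were kept per centre, a local tally would suffice for completed blocks.

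Some stronger readings are tempting but unsupported:

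- A reader might infer that concealment is absent or that the protocol's statement is false. It is secured for most patients and unsecured only near block ends.
- A reader might blame the 50% guess rate on the fixed size. It comes from balanced blocking in general, and varied short blocks make it worse (about 55% with sizes 3, 6 and 9).
- A reader might take the remark in Eligibility criteria about patients being able to follow the programme, for example with a tablet, as a discretionary criterion. It explains why CDR 0.5 or 1 is required and is not itself a criterion.

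**Conclusion.** The point holds as a minor design weakness. Because the block size is constant and published and past arms become known, the design does not by itself secure the assurance for the 15th place of each block, and sometimes the 14th. The exposure runs from near 0 of 75 (each centre sees only its own patients from one unstratified list) to 6.8 of 75 (9%; full tally shared, boundaries known), with an arm excluded for up to about 18 of 75. The article does not show where in that range the trial lies. Nothing in it shows that allocations were predicted or patients steered, and no such inference should be drawn. The sample size is unaffected.

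**What to change.** For the list, or for the part not yet used, draw randomly varying but long block sizes, for example 12, 15 and 18. Choose them to total 75 (such as 12 + 15 + 15 + 15 + 18, in random order) so that 25 per arm is kept. Withhold the sizes, including the set of candidate sizes, from enrolling staff. In the protocol, replace the stated size with a sentence saying only that block sizes vary and are withheld. Do not use blocks of 3, 6 or 9.

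The cost is a small change to the list generator and one sentence in the protocol. Two limits should be accepted openly. Balance at interim looks becomes approximate between block ends, and interim balance is one of the article's reasons for blocking. The end of the list stays partly predictable as long as the total of 75 with 25 per arm is known. The general guessing advantage from balanced blocking also remains.

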#### Informed consent

Each participant assessed will be asked to sign the agreement to the scientific analysis of the clinical data collected at the screening phase; participants enrolled in the intervention phase of the study will be asked to sign the written informed consent.

#### Withdrawal

Patients having acute organic events or manifesting the need for pharmacological treatment during the training will be excluded from the study.

Participants who no longer wish to participate in the trial may withdraw at any time without further explanation. To perform intention-to-treat analyses with as little missing data as possible, the investigator may ask the participant to use data already collected and whenever possible, the participant will be asked for permission to obtain data for the primary outcome measure.

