### Outcome measures

#### Primary outcome measure

The primary measure implemented for the present study will be the MMSE (normed total) [39].

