### Study timeline

**T0 (Baseline):** The Neurophysiopathology and Psychology Units will collect and assess clinical and diagnostic data available at baseline, together with the inclusion and exclusion criteria, to proceed with the participant selection. Measures required by the study will be therefore administered (See Table 1). Participants will therefore be randomized into three groups (Figs 1 and 2).**T1 (Post-training):** the outcome measures will be administered after 8 weeks of training.**T2 (Follow-up):** the outcome measures will be furtherly administered 3 months after the end of the training.

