#### Statistical analysis

Data will be analyzed on the intention-to-treat (ITT) principle. Missing data will not be replaced. Prior to analysis, the normality of the data will be checked by the Shapiro-Wilks test, and an attempt will be made to convert non-normally distributed variables into normally-distributed variables using appropriate variable transformations (logarithmic transformation, square root transformation, reciprocal transformation, power transformation). Descriptive statistics will be reported as mean ± standard deviation for continuous variables and as N (percent frequency) for discrete variables. Between-group comparisons will be carried out by one-way analysis of variance (ANOVA) and by the Chi-squared test for continuous and categorical variables respectively. A significant result from ANOVA will be followed up by post-hoc analysis (Tukey HSD). The effect of treatment over time for the variables under consideration will be investigated by a two-factor repeated measures ANOVA, the first factor being TREATMENT (between factor, three groups: digital-based cognitive rehabilitation combined with motor rehabilitation, paper-based cognitive rehabilitation combined with motor rehabilitation, motor training alone), and the second factor being TIME (within factor, three measurements: baseline, post-treatment, and follow-up), with repeated measurements in the time factor. Mauchly’s test of sphericity will be used to assess the sphericity assumption and the Greenhouse-Geisser correction will be applied if appropriate. A significant result from repeated measures ANOVA will be followed up by post-hoc analysis for pairwise comparisons (Dunn-Sidak).

Between group baseline homogeneity of potential confounding variables should be guaranteed by the randomization protocol, but it will be checked before analysis. In case of significant differences, analysis of covariance (ANCOVA) will be used, adjusting for covariates that may influence the outcome.

All statistical tests will be two-tailed and a p-value <0.05 will be considered statistically significant. All analyses will be carried out using the SAS/STAT statistical package, release 9.4 (SAS Institute Inc., Cary, NC, USA) by a biostatistician from the Biomedical Engineering Unit.

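### The Withdrawal rule takes randomised patients out of the study during training with no follow-up stated, which conflicts with the planned intention-to-treat analysis

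*Protocol article*

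**What the plan says.** All references are to the protocol article.

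- **Withdrawal**, first paragraph: "Patients having acute organic events or manifesting the need for pharmacological treatment during the training will be excluded from the study". No follow-up or analysis provision is attached.
- **Withdrawal**, second paragraph: after a sentence on participants who no longer wish to take part, it continues: "To perform intention-to-treat analyses with as little missing data as possible, the investigator may ask the participant to use data already collected". It adds that permission to obtain the primary outcome will be sought where possible.
- **Statistical analysis**: "Data will be analyzed on the intention-to-treat (ITT) principle", followed by "Missing data will not be replaced". Treatment over time is tested by a two-factor repeated-measures ANOVA with baseline, post-treatment and follow-up as the three time points.
- **Study timeline**: at T0, "Participants will therefore be randomized into three groups". At T1, "the outcome measures will be administered after 8 weeks of training". T2 is 3 months after training ends.
- **Sample size**: efficacy is the MMSE at the end of treatment minus the MMSE at enrolment. The size is 63 evaluable patients, raised to 75 for up to 16% drop-out.

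**The concern.** An intention-to-treat analysis needs outcomes on all randomised patients, in the arm to which they were assigned. A rule that removes patients for something that happens after randomisation works against that, and more so when the plan neither states follow-up for them nor replaces missing values.

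The two triggers are not obviously neutral. Patients are aged 65 to 80, have a vascular or multi-aetiology neurocognitive disorder, and come from cardiology, nephrology, respiratory and similar clinics. An acute illness or a newly needed drug could plausibly accompany a change in cognition, mood or walking, which the outcome measures record. The drug trigger is not limited to any class, so it may reach many patients in a multimorbid population. If the arms lose such patients at different rates, the arm that loses more poor outcomes looks better, and the result could not fairly be reported as intention-to-treat.

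A later analysis plan cannot repair this. If T1 and T2 are not collected, there is nothing to analyse.

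**Working it through.** **1. Order of events.** Randomisation (T0), then 8 weeks of training, then T1, then T2. The exclusion rule operates during training. A patient removed under it has a T0 MMSE but, if the rule is followed literally, no T1 or T2 MMSE.

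**2. Which text covers these patients.** The exclusion sentence is a paragraph of its own. The data-retention sentence is in the next paragraph, directly after the sentence on voluntary withdrawal, and works by asking the participant. Nothing states that patients removed by the protocol are followed up.

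**3. Effect on the analyses.** The change score needs T1. A classical repeated-measures ANOVA (the plan cites Mauchly's test and the Greenhouse-Geisser correction) needs all three time points. With no replacement of missing data, an excluded patient contributes to neither.

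**4. The plan's own figures.** Inputs from the Sample size section: means 0, 0.7 and 1.4; SD 1.41; alpha 0.05; one-way ANOVA.
- Noncentrality = n × Σ(mean − grand mean)² / SD² = n × 0.98 / 1.9881.
- For n = 21 this is 10.35, with 2 and 60 degrees of freedom, and power is 80.9%. For n = 20 power is 78.7%. So 21 per group, 63 in all, reproduces.
- 63 / (1 − 0.16) = 75 reproduces. The allowance is 75 × 0.16 = 12 patients.

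**5. Power if exclusions add to other losses.** The loss rates above 16% are assumptions.

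| Total loss | Per group | Power |
|---|---|---|
| 0% | 25 | 87.8% |
| 16% (planned) | 21 | 80.9% |
| 20% | 20 | 78.7% |
| 24% | 19 | 76.4% |
| 32% | 17 | 71.0% |

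**6. Possible bias.** If a fraction q of an arm is excluded and those patients' MMSE change is D points worse than that of the rest, the arm's mean is raised by q × D. The contrast between arms A and B shifts by D × (q_A − q_B). The documents give neither q nor D, so every value here is assumed.
- 5/25 against 2/25, D = 3: 3 × 3/25 = 0.36 points, which is 0.36/1.4 = 26% of the target.
- Same counts, D = 2: 2 × 3/25 = 0.24 points, or 17% of the target.
- Equal q and equal D in both arms: shift = 0.
- Exclusions in one arm only, D from 1.4 to 4.2: 0.07 to 0.21 points at q = 5%, 0.14 to 0.42 at 10%, and 0.22 to 0.67 at 16%.

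**7. Type I error in an extreme case.** This was simulated with no treatment effect, 25 per arm, SD 1.41, a 16% event rate in every arm, and event patients dropped from one arm only. The ANOVA rejected in about 7%, 12% and 18% of trials for D = 1.4, 2.8 and 4.2. It rejected in about 5% when all patients were analysed. This is an upper illustration and not an expected value.

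**The case against.** The best defence is that leaving the trial and leaving the analysis set are different things. The rule sits under Withdrawal and does not say that data are discarded. The Statistical analysis section governs analysis and says intention-to-treat. The retention sentence speaks of the participant in general and names intention-to-treat as its purpose. The article is also condensed, and details of analysis sets are commonly left to a fuller document.

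Part of this stands. The authors may have meant only that training stops, or may have meant the retention sentence to apply to everyone, so it would be too strong to say that the two sections cannot be reconciled on any reading. But the text says neither, and a label in the analysis section does not supply outcomes that are never collected. What is at issue is a stated rule, not a detail left out.

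A reader might also draw stronger conclusions, which the documents do not support:

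- **That the exclusions are known to be outcome-related.** No event rates, reasons for starting drugs or links to MMSE are given. The connection is a reasonable inference only.
- **That the analysed set would be free of medication.** The rule concerns a need for treatment that appears during training. Nothing removes patients for drugs they already take, and the entry criterion covers only recent neurology-relevant drug interventions.
- **That events would be noticed more often in one arm.** Weekly remote checks by physiotherapist and psychologist, weekly caregiver interviews and equal training time are described for all three groups. The first-week supervision by a psychologist belongs to cognitive training, but this does not establish differential detection.
- **That the loss allowance is exhausted.** The illustration has 5 + 2 = 7 exclusions in two arms, against an allowance of 12 across three.

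**Conclusion.** The point holds as a conflict between the Withdrawal and Statistical analysis sections. As written, randomised patients with a triggering event during training leave the study without a stated T1 or T2 MMSE, and they fall out of analyses that are called intention-to-treat.

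The size of the consequence is not known. The shift of 0.24 to 0.36 points (17% to 26% of the 1.4-point target) rests on an assumed imbalance of 20% against 8% and an assumed deficit of 2 to 3 points. Against the plan's SD of 1.41, that deficit is about 1.4 to 2.1 SD, which is large. Neither size nor direction of bias follows from the documents, and balanced, equally informative exclusions would cause little or none. The stated sample size is not disputed: it reproduces, and power stays at 80.9% as long as total loss, exclusions included, does not exceed 16%.

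The reason to act is that the missing outcomes could not be recovered later, whatever the true rates turn out to be.

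**What to change.** Reconcile the two sections by separating stopping the training from leaving the study. State that, for patients who meet either trigger:

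- they are still asked for the T1 and T2 assessments, at least the MMSE, subject to consent and feasibility;
- the data-retention sentence applies to them as well as to voluntary withdrawals;
- they are analysed in the arm to which they were randomised;
- the event or drug start is recorded with its date, and an event-free analysis is reported only as supplementary.

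When training should stop is a clinical matter and is not addressed here.

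Cost: a short amendment, with a check that the consent covers continued data collection. The T1 and T2 visits already exist and the sample size does not change. Some off-training data will enter the analysis, so the estimated effect may be slightly smaller. Some visits may be missed after acute events, and because missing values are not replaced, a retained patient who misses T1 or T2 could still drop out of the repeated-measures ANOVA. The change reduces the loss of outcomes but does not remove it.
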